## Discussion

A pilot study was carried out at the Dental Service of Nantes University Hospital, considering most of the parameters that will be used for this national study. It revealed a relatively small number of patients with both anxiolysis and analgesia effects. Sixty-two percent of patients presented an anxiolytic effect, and 40% showed relative analgesia. Both effects were associated in 33% of children. These effects were among the most monitored in patients [43].

Among the 76 patients assessed, 12 attempted to extend the duration of EMONO use (16%), which was considered similar to signalling a higher appetite for the product. After bivariate statistical analysis, none of the variables collected appeared significantly associated with the extension of EMONO use.

Recruiting patients needing EMONO for dental care will not be a challenge for the partners working on the project. The main objective of this project is to evaluate the effects sought and felt by children when EMONO is used in paediatric dentistry. It does not need a precise number of subjects. On the other hand, being able to characterize patients with a higher appetite for EMONO will require 1291 patients from a subject calculation with an alpha risk of 5%. This calculation was made from the results of the pilot study.

The purpose of the study is to evaluate the use of EMONO received only at the hospital. In addition to considering elements of the subject’s medical and family histories, this evaluation includes a semi-structured interview with the subject after its consumption. Given the variability in the study population, the interview will be adapted to the child’s or adolescent’s age, maturity and comprehension skills. The subject’s parent or legal guardian may also be questioned in addition to the subject.

In paediatric dentistry, the use of EMONO in children corresponds in most cases to the first administration of a substance known for its positive effect, euphoria. It seems fundamental to us to evaluate the therapeutic and non-therapeutic effects to better estimate the benefit/risk ratio of the administration. The interest of this evaluation is such that most of the French dental service university hospitals (12/16) responded favourably and wishes to participate in this work. A national study would increase the power and ensure the representativeness of the data collection.

MEOPAeDent is the first study that proposes to evaluate the appetite for the use of EMONO in the French paediatric population in need of dental care, in addition to evaluate the effects sought and felt by children. We believe that this substance evaluation known for its very important contribution in paediatric dentistry will confirm its safety of use and justify its framework of application.

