### Study size

The evaluation of the effects sought and felt by children when EMONO is used in paediatric dentistry does not require any sample size calculation. The dental service of Nantes University Hospital manages between 8 and 10 patients eligible for research per week and has a national average of numbers supported by participating dental services.

This estimate allows a 12-month inclusion potential, which represents between 5000 and 6000 patients. Considering a ratio of one eligible patient out of three to four to include, the recruitment aim is 1300 patients. The period of inclusion was set at 12 months to ensure that the study would be proposed to a maximum of eligible patients.

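### The 1291 patients said to be needed to characterize high-appetite children matches a precision calculation for the 16% prevalence, not a calculation for the regression of associated factors

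*Protocol article*

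**What the plan says.** Secondary objective (iii), in the Abstract and Background, has two parts: to evaluate children's appetite for EMONO, and to characterize the children whose appetite is high. Statistical methods gives each part its own analysis. The first is an estimate of prevalence. The second is a multivariate logistic regression for associated factors, with socio-demographic characteristics, medical history and the effects felt as candidates.

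On size, Study size says that the main objective "does not require any sample size calculation" and then works from recruitment capacity: "Considering a ratio of one eligible patient out of three to four to include, the recruitment aim is 1300 patients". The Discussion repeats that the main objective needs no precise number, but adds that "being able to characterize patients with a higher appetite for EMONO will require 1291 patients from a subject calculation", with an alpha risk of 5%. It gives the source: "This calculation was made from the results of the pilot study". The pilot results printed there for appetite are that 12 of 76 children (16%) tried to prolong inhalation, and that no collected variable was significantly associated with doing so.

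**The concern.** A calculation for finding associated factors needs a power, an effect size and the frequency of the factor. The Discussion gives an alpha only. The stated source cannot readily have supplied the rest, since the pilot found no significant association and no effect estimate from it is reported. What the pilot does supply is a prevalence, and a precision calculation for a prevalence needs only that, a confidence level and a half-width.

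If 1291 is a precision size, the article attaches it to the wrong half of objective (iii). What is at stake is how the regression will be read. If a factor shows no association, a reader told that the study had the number needed to characterize these children could take that as evidence against an association, although the capacity to detect one was never calculated in the document. The factors listed include medical history and family situation, some of which may be uncommon, and power is lowest for uncommon factors.

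**Working it through.** **1. Reproducing 1291.** From the Discussion: prevalence 16% (12/76 = 15.8%, printed as 16%) and alpha 5%, taken as two-sided. Inferred: half-width d = 2 points.

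n = z² p(1 − p) / d² = 1.96² × 0.16 × 0.84 / 0.02² = 1290.8, rounded up to **1291**, an exact match.

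**2. How specific is the match?**

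| Variant | n |
|---|---|
| 16%, ±2 points, two-sided 5% | 1291 |
| Unrounded 12/76, ±2 points | 1277 |
| 16%, ±1.5 / ±2.5 / ±3 points | 2295 / 827 / 574 |
| 16%, ±2 points, one-sided 5% | 910 |
| Other pilot rates 33% / 40% / 62%, ±2 points | 2124 / 2305 / 2263 |

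Two-proportion formulas were also tried: 16% or 12/76 against rates from 1% to 49%; power 80%, 90% and 95%; group ratios 1 to 4; one- and two-sided; with and without continuity correction. Some totals come within 3% of 1291, but only with a comparison rate, power and ratio that the article does not state. None gives exactly 1291.

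**3. What about 1300 children can detect.** Events: 0.16 × 1300 = 208. The calculation takes one binary factor held by a share q of children (assumed), overall prevalence 16%, two-sided 5% and no clustering. For a given odds ratio, the prevalences p0 (factor absent) and p1 (factor present) satisfy (1 − q)p0 + q·p1 = 0.16. With n0 = 1300(1 − q) and n1 = 1300q:

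power = Φ{[(p1 − p0) − 1.96·SE0] / SE1}, where SE0² = 0.16 × 0.84 × (1/n0 + 1/n1) and SE1² = p0(1 − p0)/n0 + p1(1 − p1)/n1.

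Example, q = 20% and OR 1.5: p0 = 0.1482, p1 = 0.2070, SE0 = 0.0254, SE1 = 0.0274. Then (0.0588 − 0.0498) / 0.0274 = 0.33, and power is 63%.

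| Share with factor (assumed) | OR detectable at 80% power | Power, OR 1.5 | Power, OR 2.0 |
|---|---|---|---|
| 50% | 1.53 | 76% | 99% |
| 20% | 1.65 | 63% | 97% |
| 10% | 1.88 | 44% | 86% |
| 5% | 2.29 | 28% | 65% |

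**4. Sensitivity to centre, under assumed ICCs only.** With 1300 children the half-width is 1.96 × √(0.16 × 0.84 / 1300) = 1.99 points. With 12 equal centres of 108.3 children, the design effect is 1 + 107.3 × ICC. For ICCs of 0.01, 0.02 and 0.05 it is 2.07, 3.15 and 6.37, and the half-width becomes about 2.9, 3.5 and 5.0 points. The article gives no ICC, and the point does not depend on this step.

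**The case against.** **The half-width is back-calculated.** No precision target or formula is printed, the unrounded pilot rate gives 1277, and other inputs can give the same number (30% with ±2.5 points also yields 1290.8). The article condenses a fuller protocol that may hold a power calculation. This stands as a limit on certainty: the sponsor should confirm the inputs. It does not remove the point. 16% is the pilot's printed figure for appetite and 30% is not among its printed rates. If another calculation lies behind 1291, the article still states a requirement for characterization with no power or effect size attached.

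**The study is not without power.** A reader might infer that it has no ability to find associated factors. The figures do not support that. Power for an odds ratio of 2.0 is 86% or more for factors held by at least 10% of children, and 208 events give about 21 per parameter for 10 parameters or about 10 for 20. What is missing is a calculation for the regression, not all capacity.

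**1300 is an aim, not a cap.** A reader might set 1300 against 1291 and conclude that only 9 children are spare for unusable questionnaires. Study size does not support this. Its own capacity figures imply from 5000/4 = 1250 to 6000/3 = 2000 children. Those figures are also a numerical basis for the study size in their own right, so 1291 is not the only one.

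**There is no contradiction with Study size.** The statement there that no calculation is needed concerns the descriptive main objective, and the Discussion keeps the same distinction.

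**The objective is secondary.** The study is observational and descriptive, and the primary endpoint is unaffected. This stands and limits the severity.

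**Conclusion.** The point holds, at moderate severity. As printed, the Discussion presents 1291 as the number needed to characterize high-appetite children, while the number matches exactly the size for estimating their prevalence to ±2 points around 16%. The match rests on an inferred half-width, the rounded 16%, a two-sided 5% level and independent children. No power or effect size is stated for the logistic regression that does the characterizing.

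With about 208 events, factors held by 20% to 50% of children are detectable at 80% power from odds ratios of about 1.5 to 1.65. At 10% and 5% the threshold rises to 1.88 and 2.29, and power for an odds ratio of 1.5 falls to 44% and 28%. These figures assume the exposures and treat one factor at a time without clustering. A null result for an uncommon factor should therefore not be read as absence of association. The sample size, endpoints and planned model are not called into question.

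**What to change.** In the Discussion, after the sponsor has confirmed the inputs:

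- Restate 1291 as the size that gives a 95% confidence interval of ±2 points around an expected 16% prevalence of higher appetite, assuming independent children. If the inputs were different, print them.
- Remove the statement that this is the number required for characterization.
- Say instead what about 1300 children (about 208 events) can detect: odds ratios of about 1.53, 1.65, 1.88 and 2.29 at 80% power for factors held by 50%, 20%, 10% and 5% of children, with the assumptions beside them. Add that a null result for an uncommon factor is not evidence of no association.
- If a centre effect is mentioned, present it as a sensitivity under stated, assumed ICCs.

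The cost is wording only. No patients, data items or analyses are added. The stated capability for uncommon factors becomes more modest.

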## Abbreviations

ANSM: French National Agency for Medicines and Health Products Safety
CEIP-A: Centers for the Evaluation of and Information on drug Dependence
CNIL: French Data Protection Body
EMONO: Equimolar Mixture of Oxygen and Nitrous Oxide
VAS: Visual analogue scale
